Regarding adverse reactions during EEG data collection, if participants experience physiological rejection responses or resistance emotions, the researchers will immediately halt the EEG data collection. Whether to continue the experiment or not will be determined based on the participant's own willingness, ensuring their health and safety. The researchers will record the reasons for their decision. The subsequent follow-up and intervention procedures of this study will be communicated to the participants after collective discussion among the research team, and decisions will be made accordingly.

1. ***Ethical considerations. [This includes the selection of an ethics committee, approval procedures, informed consent process, registration time, and registration authority (please provide registration number after completion)]***

(1) **Selection of Ethical Committee:** The chosen ethical committee for this trial is the Medical Ethics Committee of Kunming University of Science and Technology, which is located within the institution where the trial is being conducted.

(2) **Approval Process:** Before initiating the study, the research plan, project proposal, and other pertinent documents underwent submission for approval in accordance with the required procedures of the designated ethical review committee at the research institution.

(3) **Informed Consent Process:** Prior to the initiation of the study, researchers furnish participants and authorized representatives with a printed version of the informed consent form. They also clarify any inquiries pertaining to the informed consent form, ensuring that participants and authorized representatives possess a comprehensive understanding of the content before proceeding to sign the informed consent form.

(4) **Registration Time:** The trial will be registered with the China Clinical Trial Registry after receiving approval from the Ethical Committee.

1. ***Participant recruitment. [This includes the selection of recruitment locations, recruitment methods, the screening process, and the researchers conducting the screening]***

Dedicated personnel are responsible for collecting general information from participants. The general information collected includes the following details: name, gender, age, grade, major, ethnicity, handedness, years of smoking, average number of cigarettes smoked per day, current participation in similar trials, and physical and mental health status, among other relevant factors.

1. ***Collection of general participant information. [This includes the researchers responsible for data collection and the content of the general participant information]***

(1) Recruitment Location: The recruitment will be conducted in a designated group training room located on campus.

(2) Recruitment Methods: This study will employ a combination of online and offline methods for participant recruitment. Offline methods include delivering lectures in classrooms, creating posters, distributing flyers, and employing other similar approaches. Online methods involve utilizing platforms such as Qzone, WeChat Moments, as well as campus-specific platforms like the campus BBS and school's bulletin board.

(3) Screening Process: Participants will be selected in the order of their participation and based on their compliance with the inclusion and exclusion criteria.

(4) The screening process will be performed by dedicated research personnel assigned specifically for this purpose.

1. ***Baseline measures and observed variables. [For treatment studies, observed variables may not necessarily be efficacy evaluation measures, such as height and weight, but may be related to drug dosage without direct relevance to efficacy evaluation]***

(1) **Baseline Indicators:** The baseline indicators for this study include demographic information (name, student ID, gender, age, major, ethnicity, contact information); handedness; history of mental illness or psychiatric disorders; Patient Health Questionnaire (PHQ) and Generalized Anxiety Disorder (GAD) assessment; years of smoking, average number of cigarettes smoked per day; measures of craving and smoking related behaviour, access by using QSU-Brief (Questionnaire of Smoking Urges-Brief) and Nicotine Dependency Test Scale (FTND); exhaled carbon monoxide concentration; mindfulness measures (both trait- and state- mindfulness); affect measured by PANAS (Positive and Negative Affect Schedule): VAS (Visual Analog Scale) for craving of cigarettes and emotions/affection. Impulsivity measured by using Barratt Impulsiveness Scale; brain function in pre- and post-intervention period.

(2) **Observed variables:** The measurement tools and specific content are shown in **Table 1**. The outcome level and timepoints for assessment was annotated.

1. ***Standard operating procedures. [For treatment procedures, treatment methods, treatment courses, etc.; diagnostic trial standard procedures; etiological research standard procedures; prognosis research standard procedures; epidemiological research standard procedures]***

Trained personnel rigorously adhere to the main operating procedures related to this research process. The standard operating procedures are as follows:

(1) **Procedure for EEG data collection:**

- 1. Inform the participants of relevant precautions before collecting EEG data and prepare for data collection (including software and hardware). Software refers to the professional software for connecting EEG devices to computers, and hardware refers to the necessary auxiliary devices such as EEG caps and conductive paste.
  2. Measure the head circumference of the participants to determine the size of the EEG cap to be worn (large cap: 56-60cm, small cap: 54-58cm).
  3. If the participants have long hair, tie it up with a headband before wearing the EEG cap to expose both ears (participants can prepare their own headbands, or they can be provided by the laboratory).
  4. Wear the EEG cap correctly on the participant's head according to the front and back of the cap and the electrode positions (the side with letters facing up, with the letter "F" indicating the front and the letter "O" indicating the back).
  5. Measure the distance from the nasion to the inion and adjust the EEG cap back and forth to ensure that the Cz electrode is at the center of this distance. Measure the distance from the left ear lobe to the right ear lobe and adjust the EEG cap left and right to ensure that the Cz electrode is at the center of this distance. The Cz electrode should be at the intersection point of the two distances.
  6. Visually inspect the participant from the front to ensure that the EEG cap is not rotating or loosening. If there is looseness or incorrect electrode positioning, repeat step 5 until the EEG cap is properly worn.
  7. Use a special syringe (bent-tip syringe) to apply conductive paste to the corresponding channels on the scalp. Since the hair needs to be moved aside with the syringe, ask the participant about the strength of application during the process and adjust accordingly based on their response.
  8. Insert the active electrodes with labeled channels into the corresponding electrode names on the EEG cap (be careful to match the labels of the active electrodes with the EEG cap). Wrap the CMS and DRL active electrode wires around the cables of the other electrodes (wrap them 3-5 times), and plug their connectors into the corresponding ports of the amplifier.
  9. After confirming that the EEG software and hardware are properly connected, run the software for collecting EEG data. Follow the instructions of the software and confirm that the quality of the EEG data meets the standards before starting the data collection. Save the EEG data to the computer or hard drive according to the naming format.

(2) **Procedure for brief mindfulness training:** The researchers of this experiment will collaborate with professional psychology teachers for a one-week training on intervention content. Prior to each practice session, participants will be reminded of the training's schedule and location, and researchers will be present to sign in on site. The one-week training on intervention content will be conducted by professional teachers from the Students Counseling and Mental Health Center at Kunming University of Science and Technology. The training will be led by experienced psychology teachers, and the content for each day's practice will be shared with participants through their group chat for continued practice after each session.

1. ***Statistical analysis methods. [Select appropriate statistical analysis methods based on the data type of each measurement variable. Include any additional methods for subgroup analysis or auxiliary analysis. If there are personnel reductions during the trial, indicate whether an intention-to-treat (ITT) analysis was used and compare it with per-protocol (PP) analysis]***

All data will be analyzed upon completion of data collection. The data analysis process will strictly adhere to the principles of the blind method. Analysis of the data will be conducted using R software (https://www.r-project.org/), IBM SPSS Statistics for Windows, V20.0 (SPSS), MATLAB (MathWorks in Natick, Massachusetts, USA), and EEGlab (https://sccn.ucsd.edu/eeglab). Descriptive statistics will be used for demographic, psychological, and behavioural data at baseline. Two-sample t-tests and χ^2^ tests will be performed for continuous and categorical variables between the intervention group and control group. Repeated measures MANOVA will be adopted to examine intervention effects while adjusting for individual factors and pre-intervention variables (e.g., trait mindfulness and smoking indices). Within-group effects will be investigated through serial trend analysis from -T1 to T5. Linear mixed-effects model analysis will include data from all measures at different timepoints to explore factors associated with smoking cue-reactivity for both groups. EEG data will be preprocessed using Matlab software and the EEGLab toolbox. Relative spectrum power for six EEG bands (delta: 1-4Hz, theta: 4-8Hz, alpha: 8-13Hz, low-beta: 13-20Hz, high-beta: 20-30Hz, and low-gamma: 30-48Hz) will be calculated at the single electrode and ROI level. Microstate and phase synchronization analysis will be conducted, and source localization analysis will be used to investigate functional changes in subcortical brain regions. Repeated measures analysis of variance and simple effect analysis will be performed for EEG indices, considering significance in the professional field. Effect size will be measured using Cohen's d or partial eta-squared values **^[46]^**.

1. ***Participant management system.***

(1) **Contact and Guidance:** A contact group consisting of relevant researchers is responsible for providing guidance and addressing any study-related questions for participants throughout the entire study period. This ensures that participants have a clear understanding of the study and can actively cooperate with the research process. Researchers are required to respond promptly and keep records for participants who withdraw, are excluded, lost to follow-up, terminated, or suspended.

(2) **Emergency Team:** The emergency team comprises researchers and psychological teachers from the Students Counseling and Mental Health Center at the school. This team promptly identifies and addresses any participants who experience adverse reactions during the study. In cases where adverse reactions cannot be resolved, the team offers additional support and solutions to assist participants. Participants are encouraged and expected to proactively reach out to members of the emergency team if they encounter any health-related issues at any time.

(3) **Confidentiality of Information:** Any information and data obtained about participants throughout the entire study will be treated with the utmost confidentiality. Unless participants give explicit permission, no information that could identify them will be shared with individuals outside the research team. Public reports on the study results will not disclose the personal identities of the participants.

1. ***Specimen management system. [This includes the processes and systems for specimen collection, storage, and submission]***

In this experiment, the concentration of exhaled carbon monoxide (CO) is measured in parts per million (ppm) and utilized as an indicator of smoking cessation duration. The Bedfont pi CO+Smokerlyzer, a portable cigarette sensor is used to assess participants' compliance with cigarette abstinence criteria. The data collection procedure is similar to measuring breath alcohol content for cases of drunk driving. Participants exhale into the CO detector's intake port, and the device generates corresponding data, which is recorded by the researchers. If participants fail to meet the abstinence standard, they will not be eligible for EEG data collection and will need to reschedule their EEG appointment. It is important to note that the CO detected during this experiment will not be preserved or subjected to further testing.

1. ***Drug and equipment management system. [This includes the storage and distribution processes, checking systems, use, and recovery of drugs and equipment]***

This study does not involve the use of drugs or equipment management.

1. ***Data management system. [This includes data collection, management of source data and files, personnel responsible for data collection and entry, and checking systems]***

(1) **Data Collection:** The current study will strictly follow standardized operating procedures for data collection according to different data category.

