To examine the effectiveness of brief mindfulness intervention in reducing smoking cravings, this study employs a randomized controlled parallel trial design. Expanding upon existing literature that supports the positive effects of brief mindfulness interventions, the primary aim of this study is to establish the superiority of brief mindfulness intervention over the control group within the intervention conditions. The trial consists of four distinct stages: participant recruitment, baseline measurement, measurement during the intervention period, and follow-up measurement. After the completion of each stage, pertinent evaluations will be conducted to assess the outcomes. The design flowchart, depicted in **Fig 3.**, illustrates the methodology employed in this study. It is important to note that the trial has not yet begun, and it is expected that the entire process, including participant recruitment, data analysis, and article writing, will take approximately one year. Additionally, a follow-up period of one year will be conducted to assess the long-term effects of the intervention.

**
[figure not shown]
**

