**Fig 3. Study Design and Procedure**

*The upper portion of the figure illustrates the overall study design. The middle portion depicts the timeline for assessing scales and EEG at baseline, post-intervention, and follow-up timepoints. Brief mindfulness and relaxation training will be administered to both the intervention and control groups after recruitment. The baseline assessment (-T1, T0) will be completed before the intervention. Audio guidance will be provided for daily practice in the BMT group, while there will be no additional practice or intervention for the control group after training. The lower portion of the figure represents the modules of psychological and behavioural assessments during the baseline and five follow-up sessions. The cue-reactivity task will be implemented using a customized two-choice oddball paradigm. INT: intervention, rs-EEG: resting-state EEG; BMT: brief mindfulness training; VAS: Visual analogue scale; SMT: state-mindfulness.*

1. ***Sample size estimation. [List the four elements: δ(Δ) or π1, π2, α, β or Power, and provide the calculation formula]***

In this study, the subjective reports of smoking urges (QSU-Brief) will be used as the primary outcome measure. Referring to study of similar populations **^[28]^**, We set δ(Δ)_tot_ = 4 to represent the anticipated reduction of 4 points in the QSU-Brief score after the intervention in the experimental group. Multiple measurements of the QSU-Brief will be conducted on participants before and after the training, as well as during the 60-minute online training period. To estimate Cohens’d, we have set α = 0.05 and β = 0.80. Cohens’d can be calculated using the formula Cohens’d=(δ(Δ)/SD_estimate_), where the estimated SD_estimate_ was 7.65 based on reference study. Therefore, the corresponding command is pwr.t.test (d=cohens_d, sig.level = 0.05, power = 0.80, type = "paired", alternative = "two.sided"), and the estimated sample size is 34. Therefore, the minimum required sample size for the experimental group is 34. Considering a natural dropout rate of 30%, the sample size for the experimental group should be no less than 45.

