1. ***Methods of randomization and concealed allocation. [Randomization is used to reduce the risk of selection bias. Methods for generating random number sequences include computer software, random number tables, semi-random or pseudo-random methods (such as using dates, birthdays, or even/odd numbers of hospital visits). Please describe the individuals involved in generating random number sequences and the methods they use. Concealed allocation is used in treatment studies to reduce the risk of selection bias. Key steps in concealed allocation include having a designated person determine the allocation sequence, ensuring that this person is not involved in enrolling participants, and securely storing the allocation table. Please provide detailed descriptions of these steps. Central randomization is a robust method of concealed allocation. Describe the individuals and methods involved in determining the allocation sequence]***

(1) In this study, the intervention period for the BMT, which is a behavioural training, lasts for one week. Baseline data, including EEG data, will be collected from all participants. Following this, there will be a one-week training period for the intervention content, after which post-intervention data, including scales, self-reports, and EEG data, will be collected. Follow-up measurements will be conducted at 1 week, 1 month, 3 months, 6 months, and 1 year after the trial's completion. Group allocation will be performed after the completion of baseline data collection.

(2) The primary intervention method employed in this study is the brief mindfulness-based intervention of "STOP" **^[29, 30]^**, with a 7-day ~60-min sessions mindfulness course for the experimental group. Meanwhile, the control group will undergo relaxation training. All recruited participants are from the same school, and due to the lack of blinding execution conditions, achieving double-blind standards may present challenges.

(3) The randomization process for this trial will involve the use of a random sequence generator website (https://www.random.org/). This website will be utilized to ensure the random assignment of participants to either the experimental or control group.

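### The 80% power belongs to a before-after test inside the mindfulness arm, not to the between-arm superiority comparison that is the trial's primary aim

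*Protocol*

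**What the plan says.** The Study design section of the protocol states that "this study employs a randomized controlled parallel trial design" and that "the primary aim of this study is to establish the superiority of brief mindfulness intervention over the control group". The section on randomization and concealed allocation adds that "the control group will undergo relaxation training".

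The Sample size estimation section takes one outcome: "the subjective reports of smoking urges (QSU-Brief) will be used as the primary outcome measure". Its effect is "the anticipated reduction of 4 points in the QSU-Brief score after the intervention in the experimental group", and "the estimated SD_estimate_ was 7.65 based on reference study". The test is given as an R command for a paired t-test at 5% significance and 80% power ("type = 'paired', alternative = 'two.sided"). The result is that "the minimum required sample size for the experimental group is 34", raised to at least 45 for 30% dropout. Nothing is said there, or elsewhere in the protocol, about the size of the control arm, the allocation ratio, the change expected under relaxation, or power for a comparison of the two arms.

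The Statistical analysis methods section plans a repeated-measures MANOVA for intervention effects, adjusted for pre-intervention variables, two-sample tests between groups, and a mixed model using all timepoints. Within-group trends are a separate analysis.

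**The concern.** A paired test in one arm asks whether craving falls between two timepoints among people given mindfulness training. The primary aim asks whether it falls more than under relaxation. These questions differ in two ways that affect sample size. First, a difference between two independent mean changes has twice the variance of a single mean change when the arms are equal in size and spread. Second, the relevant effect is the mindfulness arm's fall minus the relaxation arm's fall, which is smaller than 4 points if relaxation helps at all.

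A reader of the sample-size section would take the trial to have 80% power for its primary aim. That figure is attached instead to a within-arm change, which cannot separate the training from time, repeated testing, regression to the mean or attention. An inconclusive between-arm result could then be misread as evidence of no advantage from a trial thought to be well powered.

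**Working it through.** **Inputs from the protocol.** Effect 4 points, SD 7.65, two-sided 5%, power 80%, stated n of 34 and then 45, dropout 30%. All are in Sample size estimation.

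**Assumptions not in the protocol.** 1:1 allocation; the full 4 points as the between-arm difference; pre-post correlations of 0.3 to 0.7. The protocol does not say whether 7.65 is the SD of change or of raw scores, so both are shown where it matters. All powers use the noncentral t distribution.

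**Step 1: the plan's own figure.**
- d = 4/7.65 = 0.523.
- Paired test: noncentrality d√n, n − 1 degrees of freedom. 80% power needs n = 30.7, so 31, not 34. Power is 80.4% at 31 and 84.1% at 34.
- Rounding d to 0.50 gives 33.4, hence 34, which may be where the figure came from.
- Dropout: 34/(1 − 0.30) = 48.6, so 49. The stated 45 matches 34 × 1.30 = 44.2, rounded up.
- 45 enrolled less 30% is 45 × 0.70 = 31.5, so 31 complete cases.

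**Step 2: the between-arm comparison, unadjusted, 7.65 as the SD of change.** Noncentrality d√(n/2), 2n − 2 degrees of freedom.

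| Analysed per arm | Power for 4 points |
| --- | --- |
| 31 (45 less 30%) | 52.6% |
| 34 | 56.5% |
| 45 (no loss by post-intervention) | 68.9% |
| 59 | 80.4% |

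80% power needs n = 58.4, so 59 analysed per arm. The difference detectable with 80% power is 5.5 points at 31 per arm and 5.3 points at 34.

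**Step 3: some improvement under relaxation.** At 31 per arm, unadjusted:
- relaxation improves by 1 point, difference 3: power 33%;
- relaxation improves by 2 points, difference 2: power 17%.

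**Step 4: adjustment for a single baseline, 4-point difference, 31 per arm.** If 7.65 is the SD of change, the residual SD is 7.65 × √((1 + ρ)/2). If it is a raw-score SD, the residual SD is 7.65 × √(1 − ρ²).

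| Assumed ρ | 7.65 is SD of change: residual SD, power | 7.65 is raw-score SD: residual SD, power |
| --- | --- | --- |
| 0.3 | 6.17, 71% | 7.30, 56.5% |
| 0.5 | 6.63, 65% | 6.63, 65% |
| 0.7 | 7.05, 59% | 5.46, 81% |

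The two readings move in opposite directions as the correlation rises, so the protocol's silence on the type of SD matters.

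**The case against.** A reader might infer that the trial has only about 53% power and would miss a true 4-point advantage nearly half the time. The protocol does not support that as a flat statement. It requires 1:1 allocation, 7.65 as the SD of change, an unadjusted test, and the whole 30% loss occurring before the analysed timepoint. The protocol fixes none of these. It plans an adjusted analysis, and it does not say when the 30% is lost in a schedule that runs to one year. With 45 per arm and no loss by the post-intervention visit, unadjusted power is 69%, and the Step 4 formulas with 7.65 as the SD of change give 76% to 86%. With 7.65 as a raw-score SD and a correlation of 0.7, even 31 per arm reaches about 80%. This much of the objection stands: the shortfall is a range, and some combinations of assumptions remove it. But those cases all credit relaxation with no benefit, the protocol states no correlation, and a raw-score SD would be the wrong divisor in the paired command that it prints.

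A reader might also infer that the plan means to claim success from the mindfulness arm's own improvement. That does not follow either. The analysis section already plans adjusted comparisons between groups and keeps within-group trends separate. The defect lies in the sizing paragraph.

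Nor is this a detail left to a statistical analysis plan. The protocol gives a complete calculation, but for a different question from its primary aim.

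**Conclusion.** The concern holds. The only power calculation in the protocol is for a one-group before-after test, while the primary aim is superiority over relaxation training in a parallel trial. The 80% figure therefore says nothing about the primary comparison. This conclusion depends on no assumption.

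The size of the gap does depend on assumptions. With 1:1 allocation and all 4 points credited to the difference between arms, power at 31 analysed per arm ranges from about 53% unadjusted to about 81% under the most favourable adjusted case examined. Every figure falls if relaxation reduces craving. Separately, and whatever the design, 34 does not follow from the printed command and 45 does not follow from 34 with 30% dropout.

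**What to change.** In Sample size estimation, replace the paired power statement with the power of the between-arm QSU-Brief comparison at the enrolment intended, or with the difference detectable at 80% power (unadjusted, about 5.5 points at 31 per arm or 5.3 at 34). State alongside it:

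- the control-arm size and the allocation ratio;
- whether 7.65 is the SD of change or of raw scores;
- the timepoint of the comparison and the loss expected by then;
- the change expected under relaxation;
- any assumed pre-post correlation, with power computed for the baseline adjustment actually used. The Step 4 figures are for a single baseline and would not apply if the two baseline measurements were averaged.

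State that the superiority conclusion rests on the baseline-adjusted between-arm contrast already foreseen in Statistical analysis methods, and that within-arm changes are descriptive.

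In the same edit correct the arithmetic: the printed command gives 31, and 34 inflated for 30% dropout is 49.

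This is a change of wording. It needs no new data and no change in enrolment, and the protocol says that the trial has not begun. The cost is a less favourable power statement.

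### The stated inputs give a minimum of 31, not 34, and 45 recruits with 30% dropout leave 31 completers, below the stated minimum of 34

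*Protocol*

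**What the plan says.** The Sample size estimation section of the protocol takes QSU-Brief as the primary outcome measure for sizing. It sets an effect of 4 points "to represent the anticipated reduction of 4 points in the QSU-Brief score after the intervention in the experimental group" and an SD that "was 7.65 based on reference study", and it defines Cohen's d as the first divided by the second. It does not print the value of d.

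For the error rates it says "we have set α = 0.05 and β = 0.80". The R command that follows is pwr.t.test for a paired, two-sided test with "sig.level = 0.05, power = 0.80". The result is reported as "the estimated sample size is 34", and the section then calls 34 the minimum required for the experimental group.

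The last step is the dropout allowance: "Considering a natural dropout rate of 30%, the sample size for the experimental group should be no less than 45". No inflation formula is shown.

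**The concern.** The paragraph prints its inputs, its command, its result and its recruitment figure, so each step can be rerun. Two of the steps fail. The command with the stated inputs does not return 34, and 45 recruits do not yield 34 completers at the assumed dropout rate. In addition, the value labelled β is the power.

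A reader cannot tell which number the sponsor is committed to. If 34 completers are needed, the recruitment figure is too low. If 45 is right, the minimum is misstated. The completer count also bears on the analysis, because the section on participant effectiveness removes voluntary withdrawals from the analysis and leaves out data collected before a suspension.

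**Working it through.** **Inputs, all from the Sample size estimation section:** effect 4 points; SD 7.65; α = 0.05, two-sided; power 0.80; paired t-test; dropout 30%; stated minimum 34; stated recruitment 45.

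**Step 1. Effect size.** d = 4/7.65 = 0.5229.

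**Step 2. Minimum n from the stated command.** A paired t-test with n pairs has n − 1 degrees of freedom and noncentrality d√n. Solving the noncentral-t power equation at d = 0.5229 gives n = 30.68, so 31.

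| n pairs | power at d = 0.5229 |
|---|---|
| 30 | 0.790 |
| 31 | 0.804 |
| 34 | 0.841 |

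The stated 34 is not reproduced. Variants at the same d do not give it either:

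| Variant | n |
|---|---|
| Normal approximation | 29 |
| One-sided | 25 |
| Power 0.85 | 35 |
| Power 0.90 | 41 |
| Wilcoxon efficiency 3/π | 33 |
| Two-sample t-test | 59 per arm |

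Setting d = 0.50 gives n = 33.37, so 34. That is the only route found to 34, and it corresponds to an SD of 4/0.50 = 8, not 7.65.

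**Step 3. Dropout.** To finish with m completers at 30% loss, recruit m/(1 − 0.30).

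- From 34: 34/0.7 = 48.6, so 49.
- Multiplying instead: 34 × 1.3 = 44.2, so 45, which is the stated figure.
- Completers from 45: 45 × 0.7 = 31.5, so 31 whole participants. The shortfall is 34 − 31 = 3, and 3/34 = 9%.
- Largest loss at which 45 still leaves 34: 1 − 34/45 = 24.4%.

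**Step 4. Where the errors offset each other.** From the minimum that the inputs support, 31/0.7 = 44.3, so 45. On the protocol's own paired basis, 31 completers give power 0.804 at d = 0.523. If d = 0.50 was intended, 31 completers give power 0.77.

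**Step 5. Label.** Power of 0.80 means β = 1 − 0.80 = 0.20.

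**The case against.** The strongest reply is that nothing is lost. For the stated effect, SD, error rates and dropout, 45 is exactly the right recruitment figure, and 34 is merely conservative. The shortfall of three is measured against a minimum that the inputs do not support. This is correct as far as power for the paired test at d = 0.523 goes. It does not rescue the text, which states 34, calls it the required minimum, and pairs it with a recruitment figure that does not deliver it.

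Two further points are fair. The protocol shows no inflation formula, so multiplication by 1.3 is an inference, although it is the evident route from 34 to 45; the shortfall against 34 holds however 45 was obtained. Likewise, d = 0.50 as the source of 34 is a guess that fits the number.

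The figure of 45 is also worded as a floor, so recruiting 49 would comply. The floor should nevertheless follow from the minimum and the dropout rate given beside it. The β label changes no number, because the command states the power correctly.

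**Conclusion.** The concern holds. The printed inputs and command give 31, not 34. At 30% dropout, 45 recruits leave 31 completers, three (9%) below the stated minimum, and keeping 34 would take 49.

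On the stated inputs this is a failure of reproducibility and consistency, not a loss of power: the two errors cancel and the paired test keeps about 80%. A real deficit arises only if d = 0.50 was intended, in which case 45 recruits give about 77%.

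These results rest on taking 4 and 7.65 as the mean and SD of the within-person change, as the paired command requires. They say nothing about the comparison with the control group, which the study design section names as the primary aim and which this calculation does not size.

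**What to change.** Rewrite the paragraph as one consistent chain and print each step:

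- If the stated inputs stand: d = 4/7.65 = 0.523; paired n = 31; 31/(1 − 0.30) = 44.3, so recruit 45.
- If d = 0.50 was intended: state and justify it; paired n = 34; 34/(1 − 0.30) = 48.6, so recruit 49. Say that 45 recruits would leave about 31 completers.

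In either case, replace the β value with 0.20 (power 0.80) and show the dropout formula.

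While the paragraph is open, it would help to state the control-arm number and the between-arm power that these numbers give. That is a secondary request, and the arithmetic correction does not depend on it.

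The cost is one paragraph of protocol wording. The first option adds no participants; the second adds four to the experimental group (49 − 45). The study design section says the trial has not yet begun, so the change can be made before recruitment.
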